### Ethical considerations and monitoring

2.10

This protocol has been approved by the Ethics Committee of the First Affiliated Hospital of Zhengzhou University (No. 2026-KY-0016), and was registered at ClinicalTrials.gov (NCT07386834, 02/04/2026). This study will adhere to the Declaration of Helsinki. Prior to randomization, all participants must provide written informed consent. Members of the Data Monitoring Committee are independent from the sponsors and funders. They will focus on the incidence, severity, and association of adverse events, and have the right to suggest the termination of the study to the ethics committee for safety reasons.

## Discussion

3

This study is important as it will rigorously and systematically investigate the effects of oro-esophageal versus nasogastric feeding on swallowing outcomes. This study plans to include a broad sample of inpatients with ischemic stroke, focusing on both general and local swallowing function, and will track functional improvements throughout the intervention period rather than only assessing the baseline and post-intervention status. Our findings are expected to provide evidence-based support for clinical decision-making in enteral nutrition.

Gastrostomy is not widely accepted in East Asia because of its invasive nature. Oro-esophageal tube feeding offers an alternative to nasogastric feeding and is therefore worthy of investigation. Compared with nasogastric feeding, if proven to more effectively improve swallowing function, to be non-inferior in safety, and to help reduce overt aspiration or the risk of aspiration pneumonia, this will provide further support for the promotion of oro-esophageal tube feeding. This will benefit not only clinical practice but also patients’ rehabilitation outcomes and quality of life.

This study will adopt the DOSS as the primary outcome. The consideration for this choice is that the DOSS is a widely accepted, clinically intuitive ordinal scale directly associated with any decision about oral intake and tube weaning. It is routinely used in swallowing rehabilitation and aligned with real-world clinical decision-making.

It is rated based on the gold-standard instrument for dysphagia, ensuring objectivity and physiological grounding. Although the DOSS is ordinal, a one-level improvement over 14 days can represent a clinically significant shift in swallowing function in acute stroke rehabilitation. This change corresponds to reduced aspiration risk, better secretion control, earlier achievement of oral intake, and lower dependence on tube feeding. To address the limited granularity of an ordinal scale, we include the MSS, YPR-SRS, and PAS as secondary outcomes. These measures directly quantify physiological improvements in secretion pooling, pharyngeal residue, and airway protection, which may not be fully captured by DOSS alone. We further strengthen sensitivity by analyzing time to one-level DOSS improvement and time to oral intake, which can capture the speed and timing of recovery rather than only endpoint status.

Due to practical limitations, this study has several limitations. First, a gastrostomy group will not be set, which limits external validity and comparison with global standards. Future comparative studies should consider to explore the differences between oro-esophageal and gastrostomy feeding. Second, this study includes only patients with acute ischemic stroke and severe dysphagia requiring tube feeding in China. Therefore, the findings may not generalize to patients with hemorrhagic stroke, milder dysphagia, other neurological conditions, different healthcare settings, or outside China. Third, given the nature of the intervention, this study lacks blinding of participants, therapists, and some assessors. Additionally, though a summary of the core standardized components has been included, the distinctive intervention protocols of each participating center have not been presented in the Appendix, which may compromise the study’s transparency. Finally, the 14-day intervention period may be insufficient to capture meaningful neuroplastic changes and long-term functional outcomes, despite the inclusion of follow-up measures.

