### Randomization and blinding

2.3

Randomization will be performed after obtaining informed consent and completion of baseline assessments, conducted separately at each trial site hospital by independent researchers using SAS version 9.4. Stratified randomization will be performed according to the DOSS levels to randomly assign participants in a 1:1 ratio to the oro-esophageal or nasogastric groups, with a block size of 4 or 6. Randomization information will be stored in the Clinical Research Methodology Key Unit and will remain inaccessible to irrelevant people.

The interventionists and participants will be unblinded, as the feeding method is identifiable. Some assessments will be scheduled during the intervention period, and these assessors will be unblinded. The assessors for day-15 assessments will be independent and blinded, as the feeding tube will be removed after the intervention period ends.

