### Sample size

2.7

Previous studies have lacked assessments using the gold standard. Therefore, we conducted a preliminary study to determine the sample size. In this study, 48 ischemic stroke patients were randomly assigned in a 1:1 ratio to the OE and NG groups, and their baseline and day 15 DOSS scores were assessed. The sample loss rate was conservatively set at 30%. Based on the results and Cohen’s formula, at least 211 participants were required for each group. The formula is as follows:

$$n1=n2=\frac{2\times {\left(Z_{\alpha {/}_{2}}+Z_{\beta }\right)}^{2}\times \sigma^{2}}{{\left(M1-M2\right)}^{2}}÷0.7$$

In this case, the corrected *α* = 0.007, (1−*β*) = 95%. M1 = 4.00, M2 = 5.16, 
σ
=2.39. The effect size was derived from our preliminary randomized trial using FEES-confirmed DOSS scores. Given the lack of prior large-scale rigorous data using gold-standard swallowing assessments, this effect size represents a clinically plausible and realistic improvement supported by our pilot data and clinical experience. This target sample size (n1 = n2 = 211) is higher than that found in related studies retrieved from common databases such as the Web of Science, PUBMED, and CNKI. Sample size calculations based on other parameters yielded results below this value. To ensure the test power, these results were not adopted. The sample sizes in other scenarios are shown in Appendix S5.

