### Statistical methods

2.9

Generalized Estimating Equations will be used to analyze repeated measures data, including the baseline and outcome DOSS, MSS, YPR-SRS, and PAS. The analyzed effects will include time, between-group, and interaction terms. Significant interaction effects indicate that differential interventions can impact the outcomes over time. Based on the primary outcome, additional analysis will be conducted by comparing the intergroup differences in the proportion of participants who will achieve oral intake at T1, using the chi-square test. The time to improvement of one level from the baseline DOSS and the time to oral intake will be analyzed using stratified log-rank tests, with stratification by the baseline DOSS. Data from patients who do not achieve their goals will be censored at day 42. The number of overt aspiration per person over 6 weeks will be analyzed using negative binomial regression to assess intergroup differences in incidence rates. Kaplan–Meier analysis will be used to handle the occurrence of aspiration pneumonia and to plot survival function curves. Statistical analyses will be based on intention-to-treat, and multiple imputation methods will be used to address partial missing values (31). Furthermore, we plan to perform several sensitivity analyses, including per-protocol analysis using a sample that excludes dropouts, and exclusion of centers from different geographic regions, to explore the stability of the main findings. The significance level *α* has been adjusted to 0.007 based on the number of outcomes (Bonferroni). Statistical analyses will be conducted using Stata v18.0 MP.

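### The Discussion names non-inferior safety as a condition for promoting oro-esophageal feeding, but the analysis has no non-inferiority comparison, and its only significance level, 0.007, makes harm harder to detect

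*Protocol article*

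**What the plan says.** The protocol article's Discussion (section 3) lists what would support wider use of oro-esophageal feeding: a larger improvement in swallowing than with nasogastric feeding and, further, "to be non-inferior in safety, and to help reduce overt aspiration or the risk of aspiration pneumonia". This is the document's only mention of non-inferiority, and no margin, safety endpoint or decision rule goes with it.

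Statistical methods (section 2.9) analyses the number of overt aspirations by negative binomial regression for a between-group difference in rates. For pneumonia, "Kaplan–Meier analysis will be used to handle the occurrence of aspiration pneumonia" and to draw curves; no between-group test is named. Adverse events (section 2.6) are to be monitored, graded and examined for cause, with no comparison of the arms stated. On the significance level, section 2.9 says that α "has been adjusted to 0.007 based on the number of outcomes (Bonferroni"). No other level is given for any outcome.

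The sample size (section 2.7) is a superiority calculation on DOSS: "In this case, the corrected *α* = 0.007, (1−*β*) = 95"%.

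**The concern.** Two things do not fit together. The first is the kind of conclusion. Non-inferiority needs a confidence limit compared with a stated margin, and failure to find a difference is not evidence of that. The second is the direction of the multiplicity correction. Bonferroni protects against false claims of benefit. Applied to a harm outcome, it makes it easier to end with no difference found, which is the result most easily mistaken for acceptable safety.

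At stake is a sentence in the final report that could influence uptake of the method. An excess of aspiration or pneumonia that misses 0.007 could be described as non-inferior safety, and nothing in section 2.9 would stand in the way. The primary DOSS comparison is not affected.

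**Working it through.** **Where 0.007 comes from.** 0.05/7 = 0.00714, which rounds to 0.007. Seven outcomes can be counted in section 2.5: DOSS, MSS, YPR-SRS, PAS, time to one-level improvement, time to oral intake, and aspiration symptoms as one item. Counting overt aspiration and pneumonia separately gives eight and 0.05/8 = 0.00625. The stated level therefore fits a family that includes aspiration symptoms once. This is an inference from the arithmetic; the document does not list the family.

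**Inputs.** Stated: 211 per arm and 30% loss (section 2.7); 1:1 allocation (section 2.3); two-sided α, from the α/2 in the printed formula. Assumed: all safety event rates, because none is given. The printed sample-size formula with a difference of 1.16 and SD 2.39 gives 160.04/0.7 = 228.6, or 229 per arm, not 211. That is a separate matter; the stated 211 is used here.

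**Power to detect harm.** For two proportions p0 and p1 with mean p̄ and n per arm:

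power = Φ[(|p1 − p0| − z × SE0) / SE1], with SE0 = √(2p̄(1 − p̄)/n), SE1 = √((p0(1 − p0) + p1(1 − p1))/n), z = 1.960 at 0.05 and 2.697 at 0.007.

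Example, 10% v 20%, n = 211: SE0 = √(2 × 0.15 × 0.85/211) = 0.03476 and SE1 = √(0.25/211) = 0.03442.
- At 0.05: (0.1 − 1.960 × 0.03476)/0.03442 = 0.926, power 82%.
- At 0.007: (0.1 − 2.697 × 0.03476)/0.03442 = 0.181, power 57%.

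| Assumed rates | 211 per arm: 0.05 → 0.007 | 148 per arm: 0.05 → 0.007 |
|---|---|---|
| 5% v 10% | 50% → 23% | 37% → 14% |
| 10% v 15% | 34% → 13% | 25% → 8% |
| 10% v 20% | 82% → 57% | 67% → 39% |
| 20% v 30% | 66% → 37% | 51% → 24% |

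The 148 column is 211 × 0.7 = 147.7 and treats the whole planned loss as absent data. That is a lower bound, since section 2.9 plans intention-to-treat with multiple imputation.

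**What a non-significant result could conceal.** At an assumed 10% in both arms and n = 211, SE = √(2 × 0.1 × 0.9/211) = 0.0292. An observed excess stays non-significant up to 1.96 × 0.0292 = 5.7 points at 0.05, but up to 2.697 × 0.0292 = 7.9 points at 0.007. At that edge the upper 95% limit is 7.9 + 5.7 = 13.6 points.

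**If a margin were set.** With equal true rates p, one-sided 0.025 and n = 211, the power to show non-inferiority is Φ(m/SE − 1.96), where SE = √(2p(1 − p)/211). For rates of 5%, 10% and 20% it is 65%, 40% and 25% with m = 5 points, and 99.7%, 93% and 73% with m = 10 points. Both margins are illustrative only. Whether the trial could support a formal claim depends on figures the document does not give.

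**The case against.** The strongest reply is that the document commits to less than a quick reading suggests. Five parts of it deserve an answer.

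- A reader might infer that the trial plans to test non-inferiority, or will read a non-significant result as non-inferior. Neither is stated. The phrase is a conditional in the Discussion, and the objectives, outcomes, sample size and analysis contain no such hypothesis. This stands. Even so, the phrase is a stated condition for promoting the method, and the 0.007 rule is in the Methods.
- A reader might infer that 0.007 is known to govern pneumonia and adverse events, or that every safety outcome has a difference test. The text supports neither: pneumonia has no named test, and nothing places adverse events in the Bonferroni family.
- The Discussion lists reduced overt aspiration or pneumonia separately from safety, so an excess of pneumonia would not meet that further condition through pneumonia. It could still be met through overt aspiration. Section 2.6 also lists pneumonia as an adverse event, and the Introduction links its follow-up to safety, so the text is ambiguous. A significant reduction would imply non-inferiority for that outcome only.
- Much of the insensitivity comes from sample size. For 10% v 15%, power at 0.05 is only 34% with 211 per arm, so about 66% of such excesses would be missed without Bonferroni, against 87% with it. The two-proportion calculation is also a stand-in for the planned analyses.
- The independent Data Monitoring Committee (section 2.10) reviews adverse events without reference to 0.007. The risk therefore lies in how results are later worded; nothing here shows a gap in participant protection.

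An analysis plan that is not shown might set a margin. The point does not rest on its absence: this document fixes one strict level with no exception for harm.

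**Conclusion.** The concern holds in a limited form. The Discussion names a non-inferiority conclusion that no comparison in section 2.9 can deliver, and the only stated level makes harm harder to detect. At every assumed rate tried with 211 per arm, moving from 0.05 to 0.007 costs between 21 and 29 percentage points of power. At an assumed 10% rate, an observed excess of nearly 8 points could pass as non-significant.

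These sizes depend on assumed event rates, on a normal approximation for two proportions, and on 0.007 being applied to the outcome in question. The last is a reasonable inference for aspiration symptoms and is not stated for pneumonia or adverse events. That non-significance does not show non-inferiority depends on none of these assumptions.

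**What to change.** In section 2.9, state that harm on overt aspiration, aspiration pneumonia and adverse events is judged from the between-group estimate (rate ratio, hazard ratio or risk difference, as suits the outcome) with an unadjusted 95% confidence interval and its upper limit, and not from non-significance at 0.007. Keep 0.007 for any claim that oro-esophageal feeding reduces aspiration or pneumonia, because the Discussion also counts that as a benefit.

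In section 3, replace the non-inferiority phrase with a statement of no excess beyond the reported upper 95% limit. Keep the non-inferiority wording only if a justified margin for a named safety outcome is fixed before unblinded data are seen.

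The cost is wording in two sections, with no extra data or participants. A more favourable claim is given up, and the safety intervals are not adjusted for multiplicity, so an isolated apparent excess will occur by chance somewhat more often.
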